#### Implementation outcome

Penetration (primary)

Individual-level penetration is calculated as the proportion of the number of employees who register for the program divided by the total number of employees at the company. The progression criterion [35] is that over 50% of the recruited companies obtain 60% individual-level adoption. The rationale for setting this goal is that from the results of an online survey of 1000 employees at MSEs, we asked the question, “If the company you work for provided you with information about the program registering as a friend on LINE regarding information useful for mental health and work, would you be willing to do so?” Specifically, 44.8% of the respondents answered “Yes or “Fairly agree” to the question. For the second question, “Please select one app or social networking site that you are most likely to use (or most prefer) when receiving mental health or work-related information.” Meanwhile, 35% of the respondents answered “do not want to receive such self-care information.” From these results, it is assumed that the estimated participation ratio would be 45–65% and that 60% of the company’s own employees would be registered as friends on LINE, which would be considered a high level of penetration at the individual level. If we do not achieve the progression criteria, the entire process and delivery of the program will be revised based on the findings of the present feasibility study.Fidelity of implementation strategies

The implementation strategy of online semi-structured lecture aims to increase the target action of that employers/managers of MSEs announce the intervention “WellBe-LINE” for employees in an effective manner to encourage them to participate as much as possible (Table 1). To assess the fidelity of this strategy, we will conduct interviews with employers/managers about whether they invite employees following the contents of the lecture (Yes/No).Cost of implementation strategies

Cost will be assessed through questionnaires with employers/managers. The time spent on program delivery will be assessed.Acceptability, appropriateness, and feasibility of the program

Acceptability, appropriateness, and feasibility will be measured using questionnaires and interviews with employees (users) and employers/managers. Implementation outcome scales for digital mental health (iOSDMH) will be used in a questionnaire to assess three domains of implementation outcomes [24]. The iOSDMH has three versions (i.e., users, providers, managers, and policymakers). The items of the iOSMDH were developed through a literature review, and the outcome was organized according to Proctor’s implementation outcomes [22]. The response options include a 4-point rating for users and 5-point rating for providers and for managers or policy makers, with the added option of “Don’t know.” In this study protocol, employees will then be asked to use iOSDMH for users and employers/managers by iOSDMH for providers. If employers and managers (or people who are concerned and provide the program in the company) are clearly separated, iOSDMH will be used by managers, policymakers, and providers, respectively.

#### Health outcome

Users’ psychological distress

Psychological distress will be measured using K6 (Kessler 6) [51, 52]. Respondents will be asked to report how frequently they had experienced the following six symptoms in the past 4 weeks: felt nervous, hopeless, restless or fidgety, worthless, depressed, and felt that everything was an effort. Response options include “none of the time,” “a little of the time,” “some of the time,” “most of the time,” and “all of the time. Scores range from 0 to 24. The Japanese version of the K6 exhibits good reliability and validity [53]. K6 works well as the CIDI Short Form in identifying cases of clinically significant mental disorders [52]. Scores over 5 are judged as having moderate psychological distress and can be used as a cutoff point for high or low distress [54, 55]. Reduction of the scores of psychological distress is a commonly used outcome in preventive interventions in the mental health field because it leads to reducing the risk of incidence of psychiatric disease [56].Work performance (HPQ)

Work performance will be evaluated using one item of the WHO Health and Work Performance Questionnaire (HPQ) [57]. Participants will then be asked to rate their overall work performance over the past 4 weeks. Items are scored on a 10-point scale ranging from 0 (worst) to 10 (best), with high scores indicating good work performance. The Japanese version of the HPQ exhibits good reliability [58].Work engagement (UWES-3)

In the ultra-short form of the Utrecht Work Engagement Scale, three items (UWES-3) will be used to assess work engagement [59]. The UWES-3 consists of three subscales (i.e., vigor, dedication, and absorption) with each of one item. The UWES-3 is a self-reported 7-point rating scale (0 = never; 6 = everyday). The mean score of the three UWES subscales, and total score is computed by adding the scores and dividing the sum by the number of items in each subscale. The Japanese version of the UWES-3 exhibits good reliability and validity [60].Job satisfaction

Job satisfaction will be measured using one item from the Brief Job Stress Questionnaire (BJSQ) [61] on a 4-point Likert scale. Higher scores indicated higher job satisfaction.Euthymia

Euthymia is a transdiagnostic construct for well-being and represents psychological flexibility, a unifying outlook on life, and resistance to stress [62, 63]. The euthymia scale (ES) is a 10-item index with dichotomous options (False = 0; True = 1). This results in total scores ranging from 0 to 10, indicating better euthymic state for higher scores. The Japanese version of the ES has high concurrent validity and sensitivity as a clinimetric scale [64].

#### Process outcome

Block rate

LINE accounts can reject or “block” contact from other accounts. We will assess this rate of blocking by system detection.Uncomfortable experience/harms

Uncomfortable experience/harm will be assessed using five items from the iOSDMH [24]. Time consumption, mental symptoms, induced dangerous experiences regarding safety, physical symptoms, and excessive pressure on regular learning will be measured for employees (users) in the questionnaire. Employers/managers and recruiters will be asked to rate the following item: “This program does not result in negative side effects (e.g., physical or psychological symptoms).” The response options are 4-point rating scales for users and 5-point rating scales for providers (managers or policy makers), with the added option of “Don’t know.”Adherence (completion rate)

Whether employees read or engaged with messages could not be accurately detected in LINE owing to technical limitations. Instead, we asked employees to answer four questions related to adherence in the follow-up survey: “How many times did you read the LINE message?” “How many times did you visit the website?” “Did you visit other websites when you received a notification on LINE?” and “Did you read other related articles in the website?”.

### Analysis

#### Sample size

As this is a feasibility study, a formal sample size calculation is not required [35], but we set the target sample size to maximum of 10 companies (200 employees), giving the variety of characteristics of the MSEs. We discussed with stakeholders, who collaborate the next definitive trial, about that this size is enough to proceed to it and agreed. This study protocol also aims to inform sample size in our future definitive trial, while the effect size estimates of feasibility study can be deviated [65]. This study protocol will support our decision to proceed to the next large trial and will be utilized for our revisions to the program and implementation strategy.

#### The criteria for success of feasibility

This study aims to test a set of feasibility objectives [36] (i.e., trial methods and implementation strategies (online training)). Testing the feasibility is ensured about whether the strategy works for behavioral changes of employers and providers and to improve the targeted primary implementation outcome (penetration). The decision about to proceed the next trial will be made based on the criteria of success of feasibility (i.e., the primary implementation outcome: penetration), which more than half of the participated company achieve 60% of the company’s own employee’s registration to the program. See the section of penetration (primary) in details.

#### Analysis of other quantitative data

Health outcomes will be evaluated using a paired *t*-test between pre-(T1) and post-intervention (T2) according to protocol. The effect sizes and 95% CIs will be calculated using Cohen’s *d* only for those who completed the post-intervention questionnaire. For subgroup analysis, we will conduct the same analysis in the subgroup divided by program completion (completer/non-completer) and satisfaction (satisfied/unsatisfied). Statistical significance will be defined as *P* < 0.05. IBM SPSS Statistics® version 28 will be used for all analyses.

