**Methods:**

For this study protocol, an internet- and text-based self-care intervention program using the LINE app (a popular message tool in Japan) will be prepared according to evidence-based psychoeducational topics. Based on our online survey findings, personalized algorithms will be implemented according to employees’ gender, age, and psychological distress levels. A personalized program using a popular pre-existing text app is expected to reduce employees’ burdens and be attractive to them, resulting in successful implementation outcomes and mental health benefits. A pre-post design feasibility study will be conducted on ten companies to evaluate trial methods (e.g., recruitment and procedures). The primary outcome will involve individual-level penetration, defined as the proportion of the number of employees who register for the program divided by the total number of invited employees at the company. The progression criterion to go next trial specifies that more than 50% of the recruited companies obtain 60% individual penetration, which is set based on the findings of the prior survey of employees at MSEs and of interviews of stakeholders involved in this study, and will be measured by LINE system. Finally, acceptability, appropriateness, and feasibility will be measured using internet-based questionnaires and interviews.

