### Recruitment and procedure

To activate MSEs’ employers/managers, we will use a pre-existing trustful pipe with the MSEs. Five licensed social insurance consultants (recruiters), who are patient public involvement (PPI) members, recruited MSEs that they had a relationship with. Recruiters provide the research information and invitation to demo program (short version of “WellBe-LINE” which finishes in 1 week). If the invited company is interested in participating in the research, the recruiter will provide contact information for researchers. The researchers will then coordinate with the employers/managers on the date of the online meeting (described in the next paragraph).

After the meeting, researchers provide one poster and one original clear file for each employee. Using a template, researchers will also e-mail employees to invite employees to participate in the program. The researcher will provide one “code” for each company. Employers/managers inform employees about the present research by the way they fit the company (e.g., e-mail, posters, and other ways of appealing them). Employees who participate in the program must enter the code after registering for the program via their personal LINE account. Research details will then be explained on the LINE chat, and they will provide their concert by pushing the button to start answering the baseline survey. Employees select their sex and age categories. They also answer six questions about psychological distress (measured by K6). The program automatically recognizes their characteristics (sex × age × distress [5 + high or low]) and starts the program. Employees informed the sensitive information (i.e., the private account information of LINE, psychological distress) will be securely handled by The University of Tokyo under ethical approval and will not be disclosed to the company they are employed through the announcement from the employers/managers and the printed paper material (poster). This study will include individuals with exceeding psychological distress threshold; however, it is justified following two aspects: (i) the program serves as a universal prevention and (ii) high scores of psychological distress are not the same as the psychiatric disorders, instead the reducing the scores is worth in primary preventive interventions.

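### Health outcomes are tested with an individual-level paired t-test that ignores company; if changes are correlated within companies, the CIs and P values are too optimistic

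*Protocol article*

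**What the plan says.** Under *Analysis of other quantitative data*, the article fixes three things for the health outcomes:

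- **Test:** "Health outcomes will be evaluated using a paired" *t*-test of T1 against T2.
- **Analysis set:** Cohen's *d* with 95% CIs "only for those who completed the post-intervention questionnaire".
- **Threshold:** "Statistical significance will be defined as" *P* < 0.05. The same analysis is repeated in subgroups by program completion and by satisfaction.

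Under *Sample size*, "we set the target sample size to maximum of 10 companies (200 employees") describes the intended sample. Under *Recruitment and procedure*, "Employers/managers inform employees about the present research by the way they fit the company", so the announcement is made company by company.

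Two stated uses depend on the health-outcome results. *Aims and objectives* lists showing that users' distress is not harmed, and *Study design* says that the data will help to set the power of a later cluster RCT. The article names no company term, cluster-robust standard error or ICC, and no method for registrants who do not answer T2.

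**The concern.** A paired *t*-test treats each employee's change as independent of every other employee's change. Here employees share a company and a manager, and that manager chose how to present the program. The sponsor already treats the company as the relevant unit, since the next trial is to be a cluster RCT.

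If colleagues' changes are positively correlated, the standard error of the mean change is too small for all five health outcomes. For the no-harm objective, the limit of the CI on the worsening side then lies too close to the estimate, and harm can appear to be excluded when it is not. For planning, an analysis without company yields no between-company variance of change, which a cluster design needs.

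A second, lesser issue is that only T2 responders contribute. If response is related to distress, the mean change among responders may differ from that among all registrants, in either direction.

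**Working it through.** **No figure to reproduce.** The article states no power, SD, ICC or T2 response rate for the health outcomes. What follows is a sensitivity range.

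**Inputs from the article.** A "maximum of 10 companies (200 employees") gives 200/10 = 20 employees per company. For registration, "it is assumed that the estimated participation ratio would be 45–65"%, which gives 200 × 0.45 = 90 to 200 × 0.65 = 130 registrants. At the 60% target there would be 120.

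**Assumptions.** There are 80 T2 responders in 10 companies (80/120 = 67% response at 60% penetration). The ICC of change is between 0 and 0.10. The test is two-sided and there is no true change.

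**Formulas.**
- Equal companies: design effect DE = 1 + (m − 1) × ICC, with m = 80/10 = 8.
- Unequal companies: m is replaced by Σn²/Σn. For illustrative sizes 2, 3, 4, 5, 6, 8, 10, 12, 14, 16 (sum 80), Σn² = 850 and 850/80 = 10.6.
- True error of the nominal 5% test = 2 × [1 − Φ(1.96/√DE)].
- Naive 95% half-width = 1.99/√80 = 0.223 SD of change (df 79).
- Company-level half-width, equal sizes = 2.262 × √(DE/80) (df 9).

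| ICC of change | DE equal / unequal | True error equal / unequal | Company-level half-width (naive 0.223) |
|---|---|---|---|
| 0 | 1.00 / 1.00 | 5.0% / 5.0% | 0.253 |
| 0.01 | 1.07 / 1.10 | 5.8% / 6.1% | 0.262 |
| 0.02 | 1.14 / 1.19 | 6.6% / 7.3% | 0.270 |
| 0.05 | 1.35 / 1.48 | 9.2% / 10.7% | 0.294 |
| 0.10 | 1.70 / 1.96 | 13.3% / 16.2% | 0.330 |

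Simulation of the paired *t*-test with a company effect on change agrees with these values. A *t*-test on company mean changes (df 9) kept its error at about 4–6% in every setting.

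**Range over sample size (equal companies; ICC 0.01 / 0.02 / 0.05 / 0.10).** With 45% penetration and 50% response (45 pairs, m = 4.5), the error is 5.4 / 5.8 / 7.1 / 9.2%. With 65% penetration and full response (130 pairs, m = 13), it is 6.4 / 7.8 / 12.1 / 18.6%.

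**Non-response.** The assumptions are no true change, a T1–T2 correlation of 0.6, 59% response, and response log-odds falling by 0.5 per SD of the driver. Positive values mean apparent worsening on K6.

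| Response falls with | Paired analysis | Likelihood-based, all T1 data |
|---|---|---|
| T1 distress | +0.08 SD | 0.00 SD |
| T2 distress | −0.08 SD | −0.13 SD |
| Worsening from T1 to T2 | −0.17 SD | −0.14 SD |

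The bias can go either way. Using all T1 data removes it in the first row only, and in the second row increases it.

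**The case against.** Four points on the other side carry weight.

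1. **The inflation is conditional.** Only correlation of change matters, and the article gives no ICC. Messages go to each employee's own LINE account and are chosen by sex, age and K6, not by company (*Personalization*; *Recruitment and procedure*), so a small ICC is plausible. At 0.01 the loss is minor. This stands. It limits the size of the concern but does not justify assuming that the ICC is zero.
2. **No go/no-go decision depends on these tests.** *The criteria for success of feasibility* rests progression on penetration, summarized in the abstract as "more than 50% of the recruited companies obtain 60% individual penetration". This stands in full.
3. **The article already urges caution.** *Sample size* warns about effect-size estimates from a feasibility study. *Limitation* concedes limited sample size, the lack of a control group and possible response bias. Without a control group, no analysis separates program effect from time trend. This also stands, but none of these cautions mentions clustering, and none corrects a CI that is too narrow.
4. **A mixed model on all T1 data is not a cure for non-response.** A reader might infer that the completers-only estimate is known to be biased and that such a model would put it right. The article supports neither inference. It does not say what drives T2 response, and the second non-response scenario shows the model doing worse than the paired analysis.

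Nor can this be left to an unseen analysis plan, because the article itself chooses the test, the analysis set and the threshold.

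**Conclusion.** The point holds in conditional form. The stated paired *t*-test ignores company, and for any positive ICC of change its CIs and P values are too optimistic. With 80 responders in 10 companies, true type I error is about 6–7% at an ICC of 0.01–0.02, 9–11% at 0.05 and 13–16% at 0.10. The number of responders, their spread over companies and the ICC are all assumptions.

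Clustering affects precision and does not by itself bias the mean change. A reader might go further and conclude that the standard errors are certainly wrong, or that the decision to proceed is compromised. The first needs an ICC that the article does not give, and the second conflicts with the penetration-based criterion. Bias from non-response is possible, of unknown direction and size.

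The change is worth making for the no-harm objective and for planning the cluster RCT.

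**What to change.** In *Analysis of other quantitative data*:

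1. Replace the paired *t*-test, as the basis for CIs and P values, with a cluster-aware analysis of change with small-sample degrees of freedom. Either of two will do:
   - a *t*-test on company mean changes, with df = companies − 1;
   - a mixed model with a company-by-time effect. A company intercept alone does not correct the standard error of the time effect.

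   The company-mean test is the simpler choice. In a check with 10 companies of 8, a model for change held its error (3.4–4.8%) but estimated the company variance as zero in 43% of runs at ICC 0.02 and 30% at 0.05. The company-mean test weights companies equally, so the text should say that the average company is the target. Use the same approach in the subgroup analyses.
2. Report the ICC of change with its interval for the next trial. With 10 companies it will be imprecise, and the interval should show that.
3. Compare T1 K6 between T2 responders and non-responders.
4. Add, as a sensitivity analysis only, a model using all available T1 data. State that it removes bias only if response depends on observed T1 data, and that it can increase bias if response depends on distress at T2.

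The cost is one paragraph of text and somewhat wider CIs. With 80 responders in equal companies, the half-width goes from 0.223 to 0.253 SD at an ICC of 0 and to 0.294 SD at 0.05. No extra data are needed.

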**Conclusions:**

This feasibility study will help validate the effectiveness of text-based interventions using a widely used social networking service (SNS) tool for employees in MSEs.

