### Aims and objectives

This pre-post feasibility study on a future effectiveness-implementation hybrid type 2 trial aims to evaluate the implementation trial procedures of text-based online programs in micro- and small-sized enterprises with less than 50 employees.

The objectives of this feasibility study, in preparation for a future trial, are as follows:To evaluate the feasibility of trial methods (e.g., recruitment, and procedures) and strategies by setting individual-level penetration as an indicator of successful implementation (primary outcome).To evaluate the barriers and facilitators at MSEs to increase individual-level penetration for revising the strategies.To evaluate the acceptability, appropriateness, and feasibility of the program among recruiters, employers/managers, and users.To evaluate the fidelity and cost of delivering the program to employees among recruiters and employers/managers.To ensure no harm on psychological distress of the users.

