### Measurements

Outcomes will be measured using online self-report questionnaires and interviews with participants (employees), employers/managers, and licensed social insurance consultants (recruiters). Table 2 presents outcomes measured for each stakeholder.

**Table 2 Tab2:** Quantitative measures, stakeholders, questionnaire assessment points, system detection, and interviews

	Users (employees)		Employers/managers	Licensed social insurance consultants (recruiters)
	Pre (T1)	Post (T2)	Post (T2)	Post (T2)
Implementation outcome of implementation strategies (system detection)				
Penetration (individual level)		✓		
Implementation outcome of implementation strategies (interviews)				
Fidelity			✓	✓
Implementation outcome of implementation strategies (questionnaire)				
Cost			✓	✓
Implementation outcome of the program (questionnaire)				
Acceptability		✓	✓	✓
Appropriateness		✓	✓	✓
Feasibility		✓	✓	✓
Process outcome (system detection)				
Friend block rate		✓		
Process outcome (questionnaire)				
Uncomfortable experience/harms		✓	✓	✓
Adherence		✓		
Health outcome (questionnaire)				
Psychological distress (K6)	✓	✓		
Work performance (HPQ)	✓	✓		
Work Engagement (UWES-3)	✓	✓		
Job satisfaction	✓	✓		
Euthymia	✓	✓		

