### Limitation

This study protocol has several limitations. First, the sample size may not be adequate to detect significant effectiveness in reducing psychological distress owing to the pilot nature of this study. Second, this study protocol lacks a control group; the true impact of the implementation strategy can only be determined in the next step. Third, generalizability of the study findings is limited owing to its challenges in the recruitment process. As with the definitive trial, only the MSEs which have high interests in health promotion can be the potential participants through the current recruitment process. Future studies could engage and recruit MSEs with low interests in health promotion may be required in studies with another research focus. Fourth, individual-level penetration may be affected by personal beliefs about mental health issues in the workplace (e.g., social desirability [71], fear of stigmatizations [72], concerns about negative impact at the workplace [73]). Thus, factors not related to the implementation strategy can be considered if the outcomes are evaluated. Fifth, digital interventions risk marginalizing vulnerable groups, such as people with difficulty using devices or without internet access. Ensuring the opportunity to provide the program for all employees is essential in future consideration. Sixth, we will not provide any additional supports to participants with high psychological distress since it is justified under the aim of primary prevention and the contents are relevant to reduce distress, but there still be a potential risk to make conditions worse. Seventh, this feasibility study will collect many exploratory items from participants to utilize the findings in future implementation research. Still, it may cause participants’ burden, resulting in the response bias. Although authors limit the items to as few, the potential burden should be acknowledged. Eighth, fidelity of implementation strategies is evaluated using one simple question, instead of using systematic approach, such as a checklist. Other actions of employers/managers to be achieved through the online lecture should be defined after this feasibility trial to develop a checklist.

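### The unadjusted 0.05 significance rule covers 25 health-outcome tests with no lead health outcome among them and no exploratory status, so isolated significant changes are likely by chance

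*Protocol article*

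**What the plan says.** In the Protocol article, the section Analysis of other quantitative data states: "Health outcomes will be evaluated using a paired *t*-test between pre-(T1) and post-intervention (T2) according to protocol". Cohen's d with 95% confidence intervals is to be calculated for those who complete the post-intervention questionnaire. For subgroups, "we will conduct the same analysis in the subgroup divided by program completion (completer/non-completer) and satisfaction (satisfied/unsatisfied". The rule for the whole set is "Statistical significance will be defined as *P* < 0.05".

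Table 2 (Measurements), under "Health outcome (questionnaire", lists five measures taken at both T1 and T2: K6, HPQ, UWES-3, job satisfaction and euthymia.

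Four other places bear on how these tests will be read:

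- **The criteria for success of feasibility:** the decision to proceed is "based on the criteria of success of feasibility (i.e., the primary implementation outcome: penetration", judged by a count of companies and not by a P value.
- **Aims and objectives:** health appears once, as "To ensure no harm on psychological distress of the users".
- **Study design and Sample size:** the data are to refine the intervention and the power of a later cluster RCT, and to inform its sample size.
- **Abstract, Conclusions:** "This feasibility study will help validate the effectiveness of text-based interventions".

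**The concern.** The primary outcome carries no significance test, so in practice the 0.05 threshold serves only the health outcomes. It applies at full strength to each of them, in the whole responder group and in each subgroup. The analysis section does not say which result carries weight or that the tests are exploratory.

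With this many tests, an isolated significant change is an ordinary chance event even if the program does nothing. The abstract tells readers that the study helps to validate effectiveness, so such a result could be reported as preliminary evidence of benefit and carried into the planning of the next trial.

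**Working it through.** The article gives no familywise error rate, so there is no stated figure to reproduce.

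**Inputs from the article**
- Five health outcomes, each measured at T1 and T2 (Table 2).
- Five analysis sets: all T2 responders, completers, non-completers, satisfied and unsatisfied users.
- Threshold of 0.05 per test, with no adjustment stated.
- Target of at most 10 companies (200 employees).

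**Assumptions, because the article does not state these**
- Tests are two-sided.
- There are 60 to 200 pre-post responders.
- The correlation between the five change scores lies between 0 and 0.8.
- Completion splits 50/50 or 60/40, and satisfaction 50/50 or 70/30. The two splits are either unrelated or correlated at 0.5 on a latent scale.
- There is no company clustering and no selection into subgroups, so the results show multiplicity alone.

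**Step 1. Number of tests.** 5 outcomes × (1 overall + 4 subgroups) = 25.

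**Step 2. Expected false positives with no true change on any outcome.** 25 × 0.05 = 1.25. This holds whatever the correlation.

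**Step 3. Reference values if all tests were independent.**
- Five overall tests: 1 − 0.95^5 = 0.226.
- All 25 tests: 1 − 0.95^25 = 0.723.

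The second value is too high for this plan. Each subgroup is part of the overall sample, and the two splits divide the same people.

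**Step 4. Simulation allowing for that overlap.** Five equally correlated normal change scores with mean zero were generated. Each was t-tested in the five analysis sets, with 5,000 to 20,000 replicates per setting. The ranges cover the different sample sizes and splits.

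| Correlation of change scores | At least one P < 0.05 in 25 tests | At least one in the 5 overall tests |
|---|---|---|
| 0 | 60–61% | 22–23% |
| 0.3 | 56–58% | 20–22% |
| 0.5 | 49–52% | 18–19% |
| 0.6 | 46–48% | 16–17% |
| 0.7 | 42–44% | 14–16% |
| 0.8 | 37–38% | 12–13% |

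The number of responders hardly changes these figures.

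**Step 5. Favourable changes only.** With 100 responders and splits of 50/50 and 70/30, the chance of at least one significant improvement in the 25 tests is 36%, 31%, 28% and 23% at correlations of 0, 0.3, 0.5 and 0.7.

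**The case against.** **This is an absence, and a journal article may leave such detail to an analysis plan.** That would be decisive if the article were silent. It is not: it states the tests, the subgroups and a significance rule for all of them. The point concerns that stated rule.

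**A feasibility study needs no multiplicity correction.** This stands, and none is asked for.

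**The article already tempers the results.** In part it does. It plans effect sizes with confidence intervals, warns under Sample size that feasibility estimates may be off, and lists the lack of a control group under Limitation. Its caveat about sample size, however, concerns missing a real effect, not finding a false one. The remark that "this feasibility study will collect many exploratory items from participants to utilize the findings in future implementation research" leads into participant burden and response bias. A reader therefore cannot say that the article lacks exploratory wording altogether, only that none is attached to these tests.

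**There is a lead outcome.** Penetration is the sole primary outcome, and psychological distress is the only health outcome in the objectives. It would be wrong to say that the plan has no lead outcome. What is missing is any priority among the health tests.

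**Health P values decide nothing.** For progression this is correct, since that rule uses penetration alone. A reader might also infer that a chance subgroup finding could set the target group of the next trial. The article does not support that: completion and satisfaction are known only after the program starts, and revisions are to be guided by interviews, voting and rating. What remains is the use of health data for the power and sample size of the later trial, together with the abstract's sentence on effectiveness. That sentence is loosely worded and the rest of the article frames the study as a test of trial methods, but it invites the wrong reading.

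**Conclusion.** The point holds in a limited form. The plan attaches an unadjusted 0.05 rule to 25 health-outcome tests, with no lead health test and no exploratory status. With no true change on any outcome, at least one significant result would appear roughly 40% to 60% of the time for change-score correlations from about 0.7 down to 0, and 37% to 38% of the time at 0.8. About 1.25 false positives are expected.

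It is tempting to say that a false positive is more likely than not. That is true only if the correlation is below about 0.5, and the article gives no correlation. It does not hold for favourable changes alone, where the chance is about 23% to 36%.

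The go/no-go decision and the primary outcome are untouched. The consequence is confined to how health changes are reported and used in planning the next trial. It is worth correcting because the change is only to wording and it settles what the study may claim about health effects.

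**What to change.** In Analysis of other quantitative data, replace the sentence that defines significance with a statement along these lines: all health-outcome and subgroup analyses are exploratory; pre-post changes will be reported as mean change and effect size with 95% confidence intervals, not adjusted for multiplicity; no result will be described as statistically significant or used as evidence of effectiveness.

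If the sponsor wants to keep one test, name K6 change in all T2 responders as the only health outcome tested at two-sided 0.05, since distress is the only health outcome in the objectives. Label the other four outcomes and all subgroup results descriptive.

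In the abstract's Conclusions, say that the study informs the design of the later trial that will test effectiveness.

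The cost is wording only, with no new data, participants or analyses. The sponsor gives up calling isolated secondary or subgroup changes significant.
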